**Fig. 2 Fig2:**
[figure not shown]
Trial schedule. ^*^The Seattle Angina Questionnaire (SAQ) and Short Form-36 (SF-36) will be only measured in the six hospitals selected for economic evaluation. ^#^The platelet aggregation and hypersensitivity C-reactive protein (hs-CRP) are to be tested in both control and treatment arm in one or two centers in Shanghai. ^a^Major adverse cardiovascular and cerebrovascular events (MACEs) include all-cause death, cardiovascular death, non-fatal myocardial infarction, stent thrombosis, revascularization, ischemic stroke, and rehospitalization for unstable angina. ^b^Routine tests include complete blood count, urinalysis, and stool tests. ^c^Includes levels of aspartate aminotransferase, alanine aminotransferase, alkaline phosphatase, gamma-glutamyl transpeptidase, total bilirubin, and direct bilirubin. ^d^Coagulation function includes levels of prothrombin time, thrombin time, international normalized ratio, activated partial thromboplastin time, and fibrinogen

### Sample size and data analysis

As little data on MACE rate in post-PCI patients who switch from DAPT to aspirin for about 12 months is available, we have to calculate the sample size according to the results of other studies. One registry trial reported that the annual rate of death or myocardial infarction was approximately 4.7%/year for patients who underwent successful implantation of at least one drug-eluting stent and did not received prolonged DAPT [25]. Another retrospective study indicated that the 2 year composite rate of mortality, reinfarction, and target vessel revascularization for patients undergoing primary PCI after acute myocardial infarction was 23% to 30% [26]. Though participants in our trial may have a lower rate of mortality, reinfarction, and target vessel revascularization than the retrospective study, taking other components into account, including stent thrombosis, ischemic stroke, and re-admission for unstable angina, we estimate the 12 month rate for the primary outcome measure in patients taking aspirin alone might be 21%, and that GXNT will reduce the incidence by 21%. A statistic power of 0.8 and a type I error rate of 0.05 (alpha) are chosen. According to a previous study, we assume the coefficient of intracluster correlation to be 0.002 [27] and we expect to recruit 90 patients from each cluster (hospital). Thus, a total of 3240 patients with 36 clusters (hospitals) will be needed. Considering a dropout rate of 10%, a minimum of 3564 patients is needed; for convenience of randomization, we decided to recruit 3600 patients (100 patients per hospital) and 36 hospitals (2400 patients and 24 clusters in the treatment arm, 1200 patients and 12 clusters in the control arm). Considering the uncertainty of the MACE rates in the study population, an interim analysis will be conducted when one-third of expected MACEs occur and the sample size will be adjusted according to the results of the interim analysis.

Data analysis will be conducted by Nanjing Medical University. All analyses will be performed on the individual level with adjustment for clustering and all available data from the dropouts will be included in the analysis up to the time of dropout where possible. All statistical hypothesis tests will be two-tailed and performed at a 5% significance level. Continuous variables will be presented as means and standard deviation, median or interquartile range. Categorical variables will be expressed as frequencies and percentages. Normality of relevant data will be examined using the Shapiro–Wilk test. Cluster-adjusted baseline differences between arms will be analyzed using the independent Student’s *t* test or the Mann–Whitney test for continuous variables and the Pearson *χ*^2^ test for categorical variables. All outcome measures, including the primary outcome measure, will be analyzed using a generalized linear mixed-effect model with the fixed effect being the intervention and the random effect being hospitals, to account for the potential correlation of outcomes within each hospital. Moreover, we will calculate the absolute rate reduction with 95% confidence interval as a crude estimate of the rate difference between the treatment and control groups by using the Mantel–Haenszel method. The number needed to treat for the primary outcome measure as the inverted absolute rate reduction will also be calculated. Efficacy outcomes are to be analyzed according to the intention-to-treat principle.

Safety outcomes will be assessed among all randomized patients except those who do not take any study medication or who have no safety records. The safety outcomes will be summarized and analyzed using the approach outlined.

Missing data will be accounted for by the modern imputation methods and all analysis will be conducted using SAS software version 9.4 (SAS Institute, Cary, NC, USA).

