### Data management and monitoring

Data from all participating centers will be imported into the clinical data management system (http://www.xyedc.com/OldXYEDC/). Methods will be adopted to ensure data accuracy and completeness. First, all source documents and laboratory reports will be reviewed by the study investigator and data entry staff to assure data accuracy. Second, site monitoring will be conducted by a clinical research associate to confirm protocol compliance, ethical standards, regulatory compliance, and data quality. Third, computer logic checks will be automatically run to identify such items as missing and questionable data. Forth, less common and more complicated errors will be checked manually. Identified errors will be corrected to ensure data quality.

In addition, a data safety monitoring committee independent of the sponsor will be recruited to guarantee the quality of the data and safety of the participants. If unexpected serious adverse events occur, and the data safety monitoring committee and investigators believe that GXNT will do great harm to participants, or results of the interim analysis to be conducted by the data safety monitoring committee show no trends of benefit, this study will be terminated early. Finally, an independent clinical endpoint committee will adjudicate all MACEs within the trial period and is blinded to treatment allocation.

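### The interim meant to handle an uncertain MACE rate is triggered by an event count, so it comes latest when the rate is low, and its arm-comparing results may reset the sample size with all tests left at 5%

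*Protocol article*

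**What the plan says.** Under Sample size and data analysis, the article bases the size on "A statistic power of 0.8 and a type I error rate of 0.05 (alpha) are chosen". It supposes that "the 12 month rate for the primary outcome measure in patients taking aspirin alone might be 21" per cent and that "GXNT will reduce the incidence by 21" per cent, and for clustering "we assume the coefficient of intracluster correlation to be 0.002". With 90 analysable patients in each of 36 hospitals this gives 3240, raised to 3600 for dropout.

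The same section then gives uncertainty about the MACE rate as the only reason for an interim look: "an interim analysis will be conducted when one-third of expected MACEs occur", after which "the sample size will be adjusted according to the results of the interim analysis". On the final analysis it says: "All statistical hypothesis tests will be two-tailed and performed at a 5% significance level".

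Under Data management and monitoring, the data safety monitoring committee conducts that interim. If its results "show no trends of benefit, this study will be terminated early".

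Under Outcome measures, the primary composite is counted over both the treatment and the follow-up periods, 24 months in all.

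**The concern.** Two things do not fit together.

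**Timing.** The interim exists to correct a wrong guess about the event rate. A rate below the guess is the case that leaves the trial too small. Waiting for a fixed number of events makes the check later the lower the rate, so it may arrive when recruitment is nearly or fully closed and adding patients is hardest.

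**Use of the arm comparison.** Judging whether there is a trend of benefit requires comparing the arms. The results of that same analysis then set the sample size, and nothing confines the size change to the pooled event rate. If the observed effect influences the new size and the final test is an ordinary 5% test, the false-positive rate on the side favouring GXNT is no longer 2.5%. Patients and caregivers are not blinded, so a size derived from the interim effect could also hint at that effect to the sites.

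At stake are the one safeguard for the 21% assumption and, to a lesser degree, the error rate of the primary test.

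**Working it through.** **1. The plan's own size.** Control rate p1 = 0.21; treated rate p2 = 0.21 × (1 − 0.21) = 0.1659; allocation 2:1; two-sided alpha 0.05; power 0.80. The pooled-variance formula for two proportions, without continuity correction, gives 912 control patients and 2736 in total. Design effect = 1 + (90 − 1) × 0.002 = 1.178. 2736 × 1.178 = 3223, or 35.8 hospitals of 90, rounded to 36 × 90 = 3240. The stated figure is reproduced, and it spends the whole two-sided 0.05 on the final test (a one-sided 5% test would need 2544).

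**2. The trigger.** With 3600 patients, expected 12-month events = 0.21 × 1200 + 0.1659 × 2400 = 252 + 398 = 650; one-third is about 217. Over 24 months at constant hazard: (1 − 0.79²) × 1200 + (1 − 0.8341²) × 2400 ≈ 451 + 730 = 1181; one-third is about 394. The article does not say which count is meant.

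**3. When it fires.** Assumptions, none stated in the article: uniform accrual over 18 months, constant hazards, a true 21% relative reduction, and the control rates in the first column as illustrations. Power is for 3240 patients.

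| Control 12-month rate | Month of 217th event | Enrolled by then | Patients needed before dropout | Power at 3240 |
|---|---|---|---|---|
| 21% | 11.8 | 66% | 3223 | 80% |
| 15% | 14.1 | 78% | 4806 | 64% |
| 10% | 17.4 | 97% | 7577 | 46% |
| 7% | 21.1 | 100% | 11,136 | 34% |

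With 12-month accrual the enrolled shares at 21%, 10% and 7% are 80%, 100% and 100%; with 24-month accrual they are 57%, 84% and 100%. On the 394-event reading with 18-month accrual, 89% are enrolled at a 21% rate and all are enrolled at 15% or below. The direction does not depend on the accrual assumption.

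**4. Error rate if the observed effect drives the size.** The article gives no rule, so one must be assumed: look at one-third of the information, reset the second stage to 80% conditional power at the observed trend, and use an ordinary final z test at 1.96. Simulated (millions of null trials) probability of a false positive favouring GXNT, nominal 2.5%:

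- Increase only, capped at 1.5 to 3 times plan, futility stop at any unfavourable estimate obeyed: about 2.5–2.6%.
- The same without the stop: about 2.7–3.1%.
- Size may also fall, but not below 0.66 of plan, stop obeyed: 2.9–3.0%.
- Size may fall to 0.5 of plan, cap 3 times, no stop: 3.8%.
- Size may fall almost to the interim size, cap 1.5 to 4 times, no stop: 4.4–4.9% (4.1–4.3% with the stop).

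**5. The futility stop.** Under the planned effect the final z has mean 1.96 + 0.84 = 2.80, so the interim z has mean 2.80 × √(1/3) = 1.62 and P(z ≤ 0) = 5.3%. Most of those trials would have failed anyway: power falls from 80.0% to 78.2%. With no resizing, the stop lowers the benefit-side error from 2.5% to 2.4%.

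**6. Why a pooled ICC should not be re-estimated.** All patients of a hospital are in one arm, so the treatment difference becomes between-hospital variance: (1/3)(2/3) × 0.0441² = 0.00043. Divided by 0.1806 × 0.8194 = 0.148, this adds about 0.003 to the ICC. With a true within-arm ICC of 0.002 the pooled value is therefore about 0.005 (simulated mean 0.0050, SD 0.0038). That would give a design effect of 1 + 89 × 0.005 = 1.445 and a size of 2736 × 1.445 ≈ 3950, although every planning assumption is correct.

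**The case against.** The strongest reply is that the article never says the observed effect will set the size. Its one stated reason is the event rate, which suggests a nuisance-parameter adjustment; done on pooled data, that costs essentially no type I error. The benefit check may be a separate task of the same committee. Rule, cap, blinding and futility threshold commonly sit in an analysis plan or committee charter that is not shown, and the 5% sentence is a general one. All of this stands. It is why the inflation is stated conditionally and why the absent threshold is not itself counted as an error. It does not answer the timing problem, which is fixed by the text under any resizing rule.

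A reader might go further, but the documents do not support these inferences:

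- **That the false-positive rate is roughly doubled.** The larger figures need deep cuts in size. With about two-thirds of patients already enrolled at the trigger under the planned rate (18-month accrual), such cuts are largely unavailable. A worst-case rule reaches about 6.1–6.2% on one side, but nobody has proposed it.
- **That the futility stop inflates type I error.** It lowers it.
- **That 5.3% of effective trials are lost to the stop.** The net loss of power is about 2 points.
- **That the interim also guards the ICC of 0.002.** The article names only the MACE rate.

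**Conclusion.** The concern holds, chiefly on timing. The trigger works against its own stated purpose: on a 12-month count and 18-month uniform accrual (both assumed), enrolment at the look is about 66% at a 21% control rate, 97% at 10% and 100% at 7%, while the size needed at the last two is about 7,600 and 11,100 against 3240. On a 24-month count the look is later still.

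The error-rate part is conditional and smaller. If the observed effect is allowed to drive the size, the benefit-side error is above 2.5%: barely so for increases only with the stop obeyed, and up to roughly 5% if the size may be cut freely. If the size change is meant to use only the pooled rate, this part disappears, but the article should then say so.

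This should be corrected before the interim takes place. It falls short of a defect that would by itself invalidate the primary analysis.

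**What to change.** - Re-estimate the size once, from the pooled, arm-blind MACE rate only. Keep the 21% relative reduction and the ICC of 0.002 as planned. The control rate follows from the pooled rate divided by (1 + 2 × 0.79)/3 = 0.86. Do not re-estimate a pooled arm-blind ICC.
- Allow increases only, up to a stated cap.
- Trigger the re-estimation by enrolment or calendar time, for example when a fixed share of patients has 6 months of follow-up, at a point before recruitment closes. State whether expected MACEs are counted over 12 or 24 months wherever that count is still used.
- Keep the final two-sided 5% level. If the arm comparison must drive the size, replace the ordinary final test by a combination or conditional-error test.
- Let the monitoring committee alone apply the no-trend-of-benefit criterion, as a non-binding conditional-power guideline.

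The cost is protocol wording and a short committee charter. The change does not itself add patients, though a low pooled rate would call for more, up to the cap. The downside is that the size can no longer be tuned to the observed effect.

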### Settings and recruitment

Qualified drug clinical trial institutions or tertiary hospitals across mainland China have been invited, and the first 36 hospitals to agree to participate will be included. Each hospital is expected to recruit 100 eligible patients. Patients can be recruited by screening inpatients and outpatients of each hospital, through media advertising and social media or by screening a PCI database. Potential eligible patients will be screened and assessed by trained investigators, and eligible participants will be asked to provide written informed consent.

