### Allocation

Thirty-six participating hospitals (clusters) with 3600 patients are firstly stratified by type of medication delivery (Western medical or traditional Chinese medicine hospitals), and then hospitals in each stratification are randomly allocated in a 2:1 ratio by a computer-generated, centrally controlled randomization schedule to treatment (24 hospitals with 2400 patients) or control (12 hospitals with 1200 patients) arms (see Fig. 1). All patients from one cluster will receive same intervention. Though the patients and caregivers are not blinded, the outcome assessors and data analysts are to be blinded to treatment allocation to minimize potential bias.

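### Hospital type stratifies the randomisation but is left out of the model fixed for every outcome, so standard errors can be too large and power forgone if type predicts MACE

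*Protocol article*

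**What the plan says.** Under Allocation, the clusters "are firstly stratified by type of medication delivery (Western medical or traditional Chinese medicine hospitals". Within each of these two strata the ratio of treatment to control is 2:1, which gives 24 treatment and 12 control hospitals in all. Hospital type is the only stratification factor named.

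Under Sample size and data analysis, one model serves for everything: "All outcome measures, including the primary outcome measure, will be analyzed using a generalized linear mixed-effect model". Its content is spelled out as a "generalized linear mixed-effect model with the fixed effect being the intervention and the random effect being hospitals". The same section adds an absolute rate reduction, described "as a crude estimate of the rate difference between the treatment and control groups by using the Mantel–Haenszel method". No variable is named for the Mantel–Haenszel strata. The protocol gives neither the number of hospitals of each type nor a MACE rate by type.

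**The concern.** Randomising within strata removes the difference between hospital types from the sampling variance of the treatment contrast, because both arms receive the same mix of types. A model without a type term does not know this. It assigns any between-type difference to the hospital random effect and carries it into the standard error of the intervention effect. If the types differ in MACE rate, the reported standard error exceeds the true one, the 5% test rejects less often than 5% under no effect, and the precision that stratification bought is not used.

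This is more than detail left to an analysis plan. The protocol states the fixed and the random part of the model and leaves out its only stratification factor. An analysis plan that follows the text would repeat the omission for every outcome.

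**Working it through.** **Inputs from Sample size and data analysis.** Control rate 21%, relative reduction 21% (so 0.21 × 0.79 = 0.1659 under treatment, difference 0.0441), power 0.80, two-sided 5%, ICC 0.002, 90 patients per hospital. The 2:1 ratio is from Allocation.

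**The plan's own figure.** The two-proportion formula with pooled variance under the null gives 912 control + 1824 treatment = 2736 patients. The design effect is 1 + 89 × 0.002 = 1.178, and 2736 × 1.178 = 3223. Dividing by 90 gives 35.8, so 36 hospitals and 3240 patients, as stated. Power at 1080 and 2160 patients with this design effect is 80.2%. No gain from stratification enters.

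**Adding hospital type, total ICC held at 0.002.** Let R be the share of between-hospital variance explained by type. With type in the model, the design effect is 1 + 89 × 0.002 × (1 − R). The standard error without type is larger by the factor √(1.178 / adjusted design effect). With equal strata (assumed), the between-type variance is (d/2)², where d is the difference in MACE rate, so d = 2√(R × 0.002 × 0.21 × 0.79).

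| R | d (points) | Adjusted design effect | SE ratio | Power with type |
|---|---|---|---|---|
| 0 | 0 | 1.178 | 1.000 | 80.2% |
| 0.25 | 1.8 | 1.1335 | 1.019 | 81.7% |
| 0.5 | 2.6 | 1.089 | 1.040 | 83.1% |
| 1 | 3.6 | 1.000 | 1.085 | 86.1% |

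R = 1 is the ceiling. Using the pooled rate (0.21 + 2 × 0.1659)/3 = 0.1806 in place of 0.21 gives d = 2√(0.002 × 0.1806 × 0.8194) = 3.4 points, so the maximum is roughly 3.5 points. Against the planned 80.2%, the gain available there is 86.1 − 80.2 = 5.9 points. That is an upper figure, because the unadjusted test also benefits a little from the balanced allocation. At R = 1 its power is Φ((0.0441 − 1.96 × 0.01556)/0.01475) = Φ(0.92), about 82%, which leaves a like-for-like gap of about 4 points by this formula.

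**Simulation.** 20,000 runs, 36 hospitals of 90, 18 of each type (assumed), 2:1 within type, linear analysis of hospital-level rates on t with 34 or 33 degrees of freedom as a stand-in for the mixed model.

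| d (points) | Power without type | Power with type | Type I error without type | Type I error with type |
|---|---|---|---|---|
| 0 | 77.3% | 77.3% | 4.9% | 4.8% |
| 2 | 77.6% | 79.2% | 4.7% | 5.2% |
| 3.6 | 78.9% | 84.1% | 3.5% | 5.1% |

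At 3.6 points under no effect, the mean standard error without type is 0.0164 against a true standard deviation of 0.0153. The power difference is 84.1 − 78.9, about 5 points. Levels sit below 80.2% because t replaces the normal distribution.

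**If 0.002 is instead the within-type ICC.** The between-type variance d²/4 is then added to 0.002 × 0.148 (0.148 = 0.1806 × 0.8194).
- d = 3 points: total ICC 0.0035, design effect 1.313, SE ratio √(1.313/1.178) = 1.056, type I error 3.8%.
- d = 5 points: total ICC 0.0062, design effect 1.554, SE ratio 1.149, type I error 2.4%.
- With the true standard error at 0.0160, power is about 75% and 69%, against 79% on the same basis with type in the model.
- d = 1 and d = 2 points inflate the standard error by only 0.6% and 2.5%.

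**Cost of the extra term.** With no difference between types, formula power is 76.3% on 34 degrees of freedom and 76.2% on 33.

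**The case against.** The strongest reply is that nothing in the protocol shows hospital type to be prognostic. If the types have the same MACE rate, standard error, type I error and power are the same with or without the term. Even if they differ, the error is on the safe side and the sample size does not rely on stratification. All of this stands. It makes the point one of efficiency, not validity, and conditional on a figure the documents do not give.

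The equal split is also only an assumption, since the first 36 hospitals to agree are taken. With 30 and 6 hospitals, a 3-point difference on top of a within-type ICC of 0.002 inflates the standard error by 3.1% instead of 5.6%. With total ICC held at 0.002, the split alters only the difference that reaches the ceiling (√(0.002 × 0.1659 / (30/36 × 6/36)) = 4.9 points), not the ceiling on forgone power.

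Three stronger readings are tempting. A reader might infer that standard errors are certainly too large; that needs type to predict MACE. A reader might infer that the trial falls to 75% or 69% power; those figures add between-type variance to the planned ICC, and at a total of 0.002 the unadjusted model does not fall below plan. A reader might also join "Though the patients and caregivers are not blinded" to "Potential eligible patients will be screened and assessed by trained investigators" and conclude that the model must adjust for patient covariates because of selective recruitment. The protocol suggests, but does not state, that screeners know the allocation. A covariate list is commonly left to the analysis plan, and the usual covariates would not correct selection on tongue or lip colour. That proposal is not part of this point.

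What the reply does not answer is that the model is stated in full, without the stratum, and that including it costs almost nothing.

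**Conclusion.** The point holds in conditional form. The randomisation stratum is missing from the model fixed for all outcomes, and whether the Mantel–Haenszel estimate uses it is unclear. If hospital type predicts MACE, standard errors can be too large, the test conservative and power forgone.

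Under the planned total ICC of 0.002, the standard error is overstated by 0 to 8.5% and the forgone power is 0 to about 6 points: 5.9 by formula against the planned 80.2%, about 5 in simulation. This is a gain not taken, not a shortfall against the stated 80%. A real shortfall arises only if 0.002 is the within-type ICC and the types differ by several points. The differences in MACE rate attached to these figures assume equal strata, and the simulation assumes a linear hospital-level analysis in place of the mixed model.

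**What to change.** Add hospital type (Western or TCM) as a fixed effect in the generalized linear mixed model for the primary and all secondary outcomes. State that the Mantel–Haenszel rate difference is stratified by hospital type, with a variance that allows for clustering by hospital. Make the change before any unblinded data are seen, so that the term does not look data-driven.

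The cost is one or two lines of text and one hospital-level degree of freedom (36 − 3 = 33 instead of 34), with no material loss of power if type is not prognostic. No extra data are needed, since hospital type is already known for the randomisation, and the sample size calculation can stay as it is.
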